**4.5 Recruitment**

Our recent findings suggest that about half of HIV+ men are likely to have had unprotected sex with a partner who is HIV- or of unknown sero-status75. Recruitment will be done from a clustering of venues, identified in our research, where men who have unprotected sex most or all of the time are over-represented4. Our team has found these venues to be accessible and their participants to be interested in participation in research. We do not expect HIV+ MSM to be attracted to workshops billed as being only about HIV prevention, but rather to a program with a larger sexual health agenda developed through our previous studies. We will seek, where possible, to encourage the participation of men with diverse ethno-cultural backgrounds and will call on the experience of research team and PPWG members who are themselves HIV+ members of Asian, Latin American, and Caribbean communities to assist in this process.

Advertisements will be placed in newspapers and magazines serving the gay community (e.g., *Fab, Xtra*) and PHAs (e.g., *The Positive Side*). Flyers about the study will also be given for distribution by AIDS Service Organizations, such as the AIDS Committee of Toronto and ethnoracial-specific AIDS service organizations (e.g., African and Caribbean Council on HIV/AIDS members, Alliance for South Asian AIDS Prevention, Asian Community AIDS Services) in the Greater Toronto Area. All study flyers and advertisements will describe the nature of the study and will provide the phone number and email of the study coordinator. Interested participants will be invited to come to the study office in downtown Toronto to learn more. Both the study coordinator and our two HIV+ gay male facilitators will conduct recruitment. In this setting, participants will have an opportunity to ask questions and receive additional explanation before signing a consent form. The consent form will include an explanation of the study, risks and benefits of participation, the duration and type of participation, description of the procedures, contact persons for the research including the chairs of the University of Windsor and Ryerson University Research Ethics Boards, voluntary nature of participation, and the right to withdraw without penalty.

**4.6 Setting**

All data will be collected at the AIDS Committee of Toronto in downtown Toronto. This location is an ideal site for conducting the proposed study, given its convenient location near public transit and proximity to areas in which large numbers of HIV+ MSM reside, and its familiar location for many HIV+ MSM. The setting was also carefully chosen as a location in which the intervention would be delivered in the community, as the AIDS Committee of Toronto is the largest AIDS service organization in Canada. Our research team’s preliminary community capacity building and training study, funded by an Ontario HIV Treatment Network community-based prevention research START grant, has been housed at the AIDS Committee of Toronto, making the transition to work on the present study simple and feasible. [name] have extensive experience conducting research and interviewing research participants in a variety of community settings frequented by both HIV+ MSM and therefore are familiar with logistic factors involved in conducting research with these populations. Further, [name] is a registered clinical health psychologist with over 10 years experience counselling HIV+ MSM.

**4.7 Consent procedures**

Participants who contact the study office will be asked if they have an interest in participating in the study. If participants agree to participate, an appointment will be scheduled to conduct their assessment. At this time, the study will be explained and participants will be given an opportunity to ask questions and receive additional explanation before signing a consent form. Participants then will be asked to sign an informed consent form including an explanation of the study, risks and benefits of participation, the duration and type of participation, description of the procedures, contact person for the research including the chairs of the Ryerson University and University of Windsor Research Ethics Boards, voluntary nature of participation, and the right to withdraw without penalty.

**4.8 Potential risks**

Completion of the assessments and interventions are free of risks for physical harm. However, the assessment and intervention may raise issues that may be troublesome to some of the participants. [name], the study coordinator, and the peer facilitators have previously been trained to deal with any emotional issues that may arise during the assessment and intervention. In addition, referral information (for counsellors, medical treatment or possibly other support or prevention information) will be made available to participants as needed. Research assistants will be supervised by a licensed clinical psychologist ([name]) who is experienced in working with both MSM and HIV patients. Further, the intervention is located at the AIDS Committee of Toronto, which has a large wealth of counselling and health resources for PHAs.

**4.8.1 Procedures to minimize risks**

Given the potentially sensitive nature of the information on sexual risk that may be gathered, we have a set of safeguards to minimize risks to participants that have worked well over a decade of similar kinds of research. Threats to confidentiality during the assessments will be minimized by using code numbers, not names, for assessments. At the end of data entry, data will be password-protected and backed-up on a master data file. All confidential material including code numbers and data will be kept in a locked office in locked file cabinets with limited access. The study will be submitted to the Ryerson and University of Windsor Research Ethics Boards for approval prior to assure risks are minimized. Threats to confidentiality during the intervention will be minimized by having all participants sign a form indicating that all information shared by members during the intervention will not be shared outside the group. This form is already available at the AIDS Committee of Toronto due to the many counselling and support groups that take place there. Participants also will be invited to use only their first names, or a pseudonym, as the participant prefers. Participants will not be aware of other participants’ code numbers for assessment.

**4.8.2 Risks versus benefits**

The primary risk for participation in the study is related to breaks in confidentiality. As noted above, several steps will be taken so that data will remain confidential both during and after the investigation. Another risk is the possibility that participants may become upset by the questions on the questionnaire. Although benefits to the participant are likely to be minimal, some participants may appreciate the study’s focus on mental health and its in-depth focus on what may actually be happening in sexual situations that may inhibit or promote healthy sexual behaviour.

**4.9 Monitoring and Evaluation of the Intervention**

**4.9.1. Comprehensive Dynamic Trials**

The framework of *continuous quality improvement design (CQID)*76will guide the development of monitoring and evaluation for this project. CQID is particularly well suited to interventions that are grounded within communities and social networks, that must be able to accommodate diverse needs in a heterogeneous population, and that include goals of maximizing effectiveness and responsiveness to community needs. Monitoring and evaluation in CQID are designed to collect information not only on the targeted outcomes but also on mediating factors. Data are collected from multiple sources (e.g. participants, facilitators, participation records) using multiple methods. Analysis explores patterns of outcome and response to the program, tracing pathways of influence on the thinking, choices and actions of different groups of participants, thereby providing information about how different participants interpret and respond to the intervention based on their particular personal and social locations. Information about what works in various contexts and for various people is fed back into the intervention through the study team that has representation from diverse stakeholders in order to guide modifications for enhancing the intervention’s acceptability, responsiveness to the community, and effectiveness in achieving the desired objectives. CQID takes an intervention through several iterations with monitoring and evaluation informing modifications or retooling between iterations.

**4.9.2 Mixed Method Approach: Quantitative and Qualitative Data**

Quantitative data will be collected at the study site through a battery of self-report questionnaires and interviews. Facilitators will also maintain attendance records. Based on analysis of the structured assessments and surveys at each of the three data collection points, a selection of participants will also participate in face-to-face semi-structured interviews. Participants will be selected to represent a broad diversity of experiences related to UAI, intermediary factors, and responses to the intervention. It is estimated that approximately 10 of the total sample size of N=42 participants will be randomly selected to be recruited for interviews at each of the 2 data collection points (not necessarily the same individuals at each timepoint). Interview participants will be asked to provide greater detail related to their responses to the survey, exploring in depth their opinions about the intervention they have completed.

Participants will complete brief assessments at the end of each workshop, responding to approximately 5 questions about that workshop: (a) What did you like the best and why? (b) What did you like the least and why? (c) What do you think is most useful to you? (d) Would you recommend this session to a friend? (e) Are there some people for whom this session would be particularly useful? Please describe them. Group facilitators will compile notes at the close of each session answering the following questions: (a) What went particularly well? Why? (b) What did not go as well as you had hoped or anticipated? Why? (c) What was missing that should be considered for inclusion in the future? (d) How would you assess the group dynamics? (e) What unsolicited comments were made to you about this session by participants? (f) What else do you want to say about this session?

The quantitative and qualitative data collected during the monitoring and evaluation will be analyzed both independently and in tandem, with results of each analysis informing the other. In-depth interviews will be used to further elaborate and clarify the quantitative results and will also lead to potentially new questions for quantitative analysis. Given the nature and size of the sample (42 participants), the Phase II nature of the intervention, and consistent with the CDT design, the goal of the monitoring and evaluation will be provision of information from diverse data sources that contributes to improving the intervention for our future studies.

**4.9.3 Quantitative Measures**

The quantitative measures used in this study have been demonstrated to possess good reliability and validity, as well as documented associations with risky sexual behaviour23,51,52,59,60. It is anticipated that the entire protocol will take approximately 50 minutes to complete at each timepoint: baseline, post-intervention, and 3 months after the end of the intervention.

**Demographics Questionnaire.** Participants will complete a demographics questionnaire assessing age, ethnic/racial background, religious affiliation, educational level, living situation, marital/partner status, socioeconomic status, and sexual orientation.

**Primary Endpoint Variable: Unprotected Sexual Behaviour.** Participants will be asked to indicate their frequency of unprotected anal intercourse with HIV-negative or unknown HIV status partners in the past 3 months.

**Secondary Endpoints.** Secondary endpoints will also examine protected and unprotected 1) insertive and receptive anal intercourse with men, 2) anal and/or intercourse with women with and without a condom in the previous 3 months with partners who were HIV+, partners who were HIV-negative, and partners of unknown serostatus. Second, participants will be asked to indicate their number of HIV+ partners, HIV-negative partners, and partners of unknown serostatus in the previous 3 months. Third, participants will be asked if they had insertive or receptive anal intercourse or vaginal intercourse with their last sex partner, as well as their last partner’s serostatus.

**Potential Theoretical Mediators.** Per the IMB model, Information, Motivation, and Behavioural Skills will be assessed to examine the relative effects of each component on UAI with non-HIV+ partners. The HIV-Knowledge Questionnaire-1876 will be used to assess knowledge of basic HIV information. Questions will also ask about knowledge of very recent data, such as the PHAC’s statement on the Swiss Cohort Study77, and knowledge of criminalization of unprotected sex for HIV+ individuals (CITES). Participants’ motivations to perform 8 risk-reduction actions will be assessed per recent research assessing the IMB model60. Examples of items include intentions to keep condoms nearby, to use a condom with a new sexual partner, and to use a condom when drunk or high on a substance. Self-efficacy for behavioural skills in risk reduction will be assessed using a 6-item measure60. Items include “I am certain I can use a condom with my main sex partner.” Participants will also be asked about whether they have engaged in 5 risk reduction behavioural skills over the past month, such as refusing to have unsafe sex and guiding sex toward safer sex behaviour.

**Additional Measures.** Due to data implicating substance use in unprotected intercourse among MSM**38**.**78-81**, participants will indicate how many times they have been intoxicated when drinking alcohol or used an injection or non-injection substance in the past 3 months. To assess for possible confounding due to social desirability reporting bias on sensitive behaviours such as sexual behaviour and drug use, participants will complete the Marlowe Crowne Social Desirability Scale - Short Form81. If any of these variables is associated with unprotected sexual behaviour, they will be examined as potential other mediators in analyses examining the effect of the intervention on unprotected anal intercourse with HIV-negative or unknown HIV status partners. CD4 count and viral load will be requested through self-report for the present study. These measures will serve as medical indices of severity of HIV illness in our HIV+ sample.

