**2.0 BACKGROUND AND RATIONALE**

**2.1 UAI with HIV-negative or unknown serostatus partners among HIV+ MSM**

Several studies suggest that many MSM operate under mistaken assumptions about their sexual partners’ HIV status. Many HIV+ men read the willingness of their partners to engage in UAI as itself evidence that partners are already HIV+9-18. HIV-negative men, on the other hand, may assume the opposite: that partners willing to engage in UAI “must be” negative19,20. However, these assumptions may frequently be mistaken, as 64% of partners of HIV+ persons who were perceived by participants as HIV+ were actually HIV-negative11.

Another important factor that may account for the increasing HIV prevalence among MSM in Ontario is the rise of barebacking, often defined as intentional UAI4,22. The development of sub-groups of men who bareback among HIV+ men may account for a cascade of recent evidence showing elevated and rising rates of UAI among HIV+ men with partners of unknown or negative HIV status23-37. The Ontario Men’s Survey38 found that 30% of HIV+ men reported having UAI with a partner of unknown serostatus during the previous year, and 20% with a partner they assumed to be HIV-negative. It is critical to note that while most (but not all) barebackers are HIV+, most HIV+ men are not barebackers39. Many practise safe sex and many more employ risk reduction techniques if a condom is not used. However, there is still an unmet need for empirically tested interventions to reduce sexual risk behaviour among HIV+ MSM, including those who engage in barebacking (intentional UAI) with non-HIV+ partners or who otherwise engage in UAI with non-HIV+ partners without a previous intention of engaging in UAI.

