**2.3 Guiding Model for the Intervention: The IMB Model**

**2.3.1 Elicitation research using the IMB model**. The IMB model developed by Fisher et al. (2002) will serve as the theoretical model guiding the present study’s HIV prevention intervention52. This behavioural model, supported by PHAC’s Canadian Guidelines for Sexual Health Education57, is strongly empirically supported for a variety of populations regarding HIV risk prediction and in the development of efficacious HIV prevention interventions23,58-62. The IMB model specifies that HIV prevention information and motivation are relatively independent constructs which increase HIV preventive behaviour directly and by increasing behavioural skills (e.g. effective condom negotiation) that in turn increase HIV preventive behaviour. The IMB model specifies that elicitation research must first be conducted before designing HIV prevention interventions. Elicitation research refers to research that identifies relevant information, motivation, and behavioural skills of the target population, and typically includes focus groups, interviews, and surveys. This research has already been conducted by the study team on the information, motivation, and behavioural skills of HIV+ MSM in Ontario4,14,15 and is reviewed below:

**2.3.2 Information.** This is a population that is largely well-informed about the basics of HIV transmission and pathogenesi**s**59 and typically already in treatment. Based on our own research4, as well as that of others, HIV+ men need advanced information that could help them in their decision making processes regarding HIV risk, including: 1) the relationship between viral load and transmission59, 2) solutions to erectile problems10,63,64, 3) unprotected sex and acquisition of alternative strains of HIV, syphilis, LGV, hepatitis C, etc, 4) the risk of top or bottom roles in sex and the risk of sex with another HIV+ person4, 5) risks of presuming or intuiting a potential partner’s sero-status, and 6) the current legal context in Canada in which unprotected sex without disclosure may be considered a crime65.

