**2.3.3 Motivation**. For this set of men who have unprotected sex much of the time, motivation is a critically important area to address. Men with bareback practices demonstrate inconsistent motivations regarding engaging in unprotected anal intercourse. For example, although they fairly consistently engage in UAI and are aware of risk of HIV transmission, few, if any, wish transmission to occur and most, if not all, articulate their desire to actively avoid transmission. Many also express a desire to give back to the gay community and to protect younger or uninformed men14.

**2.3.4 Behavioural skills.** While the central focus for risk reduction will be on condom use in anal intercourse, research documents the complex array of behaviours and skills required for consistent condom use47-49, 58. Based on the extant literature, it is anticipated that this intervention will address: (a) HIV-status disclosure skills; (b) negotiation of safer sex practices; (c) exploration of nonpenetrative sex alternatives; and (d) experimentation with a variety of condoms to enhance the condom-wearing experience, in a context of expanding ideas of what may be desirable and how to have sexy, satisfying, and intimate relations. Behavioural skills are typically delivered using both role play of behavioural skills and identification of high-risk situations (e.g. substance use, depression). Behavioural skills approaches can be integrated into motivational approaches to create efficacious interventions, and have been used in previous studies with heterosexual populations58.

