**2.4 Intervention Implementation**

**2.4.1 The Intervention Implementation Model: Motivational Enhancement Counselling**

Per the IMB model, the study intervention will specifically address HIV prevention information, motivation, and behavioural skills. The intervention implementation model, will build directly from the IMB theoretical model using motivational enhancement counselling53,55,58,59. Motivational enhancement counselling is designed to induce rapid, internally motivated change by using the participants’ own change resources58,60. The specific steps include: 1) eliciting from the participant his ideas about how a behaviour can be changed, 2) enhancing the participant’s confidence in being able to make the desired change, while 3) constantly attempting to help the participant locate and express his own reasons for wanting to change53. Motivational enhancement counselling also tailors the intervention toward a participant’s stage of readiness to make change54,66. Considering the recurrence of social isolation as a theme in the narratives of risk-taking men38,53,68-70, the intervention will also be designed as a small group counselling session to help foster social interaction among participants. A major difference between the small group intervention for HIV+ MSM described by Wolitski et al (2004) and the small group intervention in the current study is the intervention implementation model. The unsuccessful SUMIT intervention used social cognitive theory, which posits that people make change when given sufficient information and behavioural skills68,71,72. In contrast, the intervention in the present study does not assume that information and behavioural skills are sufficient to make change, and instead relies also on helping participants to find their own internal motivations to engage in behavioural change. Motivational enhancement counselling is also a goal-directed counselling style that has been shown to be effective in reducing sexual transmission risk behaviour for primarily HIV-negative samples of MSM and high-risk heterosexuals60,62.

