**4.2 Overview of the Study Design**

Written informed consent will be obtained prior to study enrolment including permission to complete study measures. Those who agree to enrol and meet inclusion criteria will be scheduled for a single assessment session to complete a demographics questionnaire, self-report measures, and a brief interview. Participants will complete 6 sessions of a small-group sexual health intervention to reduce sexual risk behaviour. Assessments will be conducted at the completion of each 6-session group, with follow-up assessments conducted at post-intervention and at 3 months following the end of each group.

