**4.3 Sample**

Individuals will be eligible to participate in the intervention if they: (1) are HIV+ men who report UAI with a partner of HIV-negative or unknown HIV status in the past 3 months; (2) speak and understand English, (2) anticipate that they will be able to attend all workshops; and (3) are willing to participate in program monitoring and evaluation. Persons will be excluded if it is found that their ability to respond to study measures could be compromised by 1) central nervous system conditions (e.g., advanced HIV-associated dementia), 2) acute psychotic conditions, 3) acute mood dysregulation (e.g., manic states), and/or 4) debilitating physical conditions. For ethical reasons, all participants may withdraw from the research component of the study while still remaining in the intervention. Based on the literature, we anticipate that a number of participants will display psychological or other lifestyle characteristics that are strongly associated with sexual risk taking. They will be offered referral to counselling where appropriate; however, the decision to pursue such additional support will be left with the individual men and will not influence their eligibility to participate in the intervention. To avoid conflict of interest, participants who are given referrals will be referred to counselling with providers outside the study team. In addition, if a participant experiences distress at any time, referrals for counselling will be ready at hand. Intervention program facilitators will be trained in group facilitation and will be knowledgeable about referral sources for HIV+ group members who seek information or counselling, and the project will be housed at the AIDS Committee of Toronto which has HIV-related counselling and information resources.

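### The primary endpoint depends on the partner's serostatus as the participant reports it, with no rule separating known from presumed status, so the pre-post change can mix behaviour with relabelling

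*Protocol*

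**What the plan says.** **Endpoint.** Protocol 4.9.3, primary endpoint: "Participants will be asked to indicate their frequency of unprotected anal intercourse with HIV-negative or unknown HIV status partners in the past 3 months". Protocol 4.3 admits men who "are HIV+ men who report UAI with a partner of HIV-negative or unknown HIV status in the past 3 months". If the count cannot be normalised, 4.10.3 falls back to presence or absence of unprotected sex with non-HIV+ partners over the same period. All three use the same partner classification, and none says how a partner's status is to be established.

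**Presumption.** Section 2.1 states that many HIV+ men take a partner's willingness to have UAI as a sign that he is already HIV+. It then cites a study in which "64% of partners of HIV+ persons who were perceived by participants as HIV+ were actually HIV-negative".

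**Intervention.** Section 2.3.2 lists six information needs. The fifth is the "risks of presuming or intuiting a potential partner"'s serostatus. Section 2.4.1 says that "the study intervention will specifically address HIV prevention information, motivation, and behavioural skills". Section 2.3.4 puts "HIV-status disclosure skills" first among the skills to be addressed.

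**Design.** Section 4.2: "Participants will complete 6 sessions of a small-group sexual health intervention to reduce sexual risk behaviour". Everyone receives the intervention, and no concurrent control is described.

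**The concern.** The endpoint is a count of acts filtered by a belief about the partner, and the intervention may change that belief. A man may report a partner he presumes to be HIV+ under HIV+ at baseline, so that UAI with him lies outside the endpoint. If he later comes to doubt such presumptions, he may report the same kind of partner as unknown, and the same act then enters the endpoint. A control arm would not fully solve this, but here there is none, and nothing in the primary endpoint separates a change in acts from a change in labels.

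The stake is the study's main product. Sections 1.0, 3.0 and 5.0 make the effect size the purpose of the trial and the basis for a later randomised trial. The mediator analysis in 4.9.3 is exposed too, because the men who absorb most information may be those who relabel most.

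**Working it through.** The plan gives no figure on this point to reproduce, and the sample size in 4.4 does not bear on it. The check is a reading of the text followed by arithmetic on assumed values.

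**1. Is the mechanism in the text?** The endpoint uses reported partner status (4.9.3). Reported status is often presumed and often wrong (2.1). Presumption is a listed information need (2.3.2), and the intervention addresses information (2.4.1). Section 2.4.1 places that component mainly in sessions 1 and 2, before both follow-up assessments. Each link is stated except the last: that men will relabel partners on the questionnaire is an inference.

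**2. How much could it move a count?** Notation:
- A: baseline UAI with negative or unknown partners.
- k: baseline UAI with presumed-HIV+ partners, divided by A. Assumed; not in the protocol.
- f: share of presumed-HIV+ UAI reported as unknown at follow-up. Assumed; not in the protocol.
- RR: true follow-up/baseline ratio of UAI, taken as equal for both partner types. The value 0.80 is the meta-analytic figure in 2.2, used only as a benchmark.

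Follow-up endpoint = RR·A + f·RR·k·A, so the observed ratio = RR × (1 + f·k).

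| k | f | observed, RR = 1 | observed, RR = 0.80 |
|---|---|---|---|
| 0.5 | 0.10 | 1.05 | 0.84 |
| 0.5 | 0.25 | 1.125 | 0.90 |
| 0.5 | 0.50 | 1.25 | 1.00 |
| 1 | 0.10 | 1.10 | 0.88 |
| 1 | 0.25 | 1.25 | 1.00 |
| 1 | 0.50 | 1.50 | 1.20 |
| 2 | 0.10 | 1.20 | 0.96 |
| 2 | 0.25 | 1.50 | 1.20 |
| 2 | 0.50 | 2.00 | 1.60 |

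A true 20% reduction disappears when 0.80 × (1 + f·k) = 1, that is f = 0.25/k: 50% at k = 0.5, 25% at k = 1 and 12.5% at k = 2.

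**3. The opposite shift.** Let s be the share of negative/unknown UAI that is reported under known HIV+ at follow-up because status was disclosed. The observed ratio becomes RR × (1 + f·k − s). With f·k = 0.25 and s = 0.25 the two shifts cancel. With f = 0 and s = 0.20, unchanged UAI (RR = 1) is observed as 0.80. A move from unknown to known HIV-negative has no effect, since both count in the endpoint. So the sign depends on f·k against s, and the protocol gives none of the three.

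**4. Dichotomised fallback.** Eligibility already requires qualifying UAI in the past 3 months, so baseline presence is about 100% if screening and baseline reports agree. Relabelling cannot raise it. It can only keep a man classed as present at follow-up who, under his baseline labels, would be classed as absent.

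**5. Under a fixed rule.** If presumed-HIV+ partners count as unknown throughout, baseline is A(1 + k) and follow-up is RR·A(1 + k). The ratio is then RR for any k, and f drops out. Total UAI with men is unaffected by any move between categories, including s.

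**The case against.** The strongest case on the other side has five parts.

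- **The questionnaire is not shown.** Section 4.10.1 promises a manual covering eligibility and the administration of measures, where a respondent instruction could sit. That is fair, and the protocol states no wrong rule. But it does fix the primary endpoint and eligibility on a classification that it leaves open, and no analysis plan can recover how status was established if the question never asked.
- **Relabelling is inferred.** A reader might infer that the sessions teach men not to presume and that they will therefore relabel. The documents do not go that far. Section 2.3.2 states a need and speaks of potential partners, not the labelling of past ones, and the outline of the informational component in 2.4.1 does not list presumption. *May be relabelled* is the most the text supports.
- **The direction is not fixed.** A reader might infer that the bias runs against the intervention. That describes one pathway. Disclosure skills can lower the endpoint, although asking and telling are themselves behaviour changes that the programme seeks.
- **The size is assumed.** The pair f = 25%, k = 1 offsets 0.80 exactly; it shows what would be needed, not what will happen. The 64% comes from one cited study and is not an estimate for this sample.
- **The data to see a shift are already planned.** Section 4.9.3 collects acts and partner numbers by status. This stands, and it makes the remedy cheap. But the protocol does not tie those data to the interpretation of the primary endpoint.

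Leaving UAI with HIV+ partners outside the endpoint is a choice of scope and is not criticised here.

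**Conclusion.** The point holds as a weakness in how the primary endpoint is measured. Eligibility, the primary count and the fallback dichotomy all rest on reported partner status with no rule for presumed status. The protocol itself describes presumption as common, error-prone and a subject for the intervention. A single-arm change from baseline can therefore mix behaviour with relabelling.

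Neither the net direction nor the size can be known from the documents. The table in the working is illustrative: it rests on assumed f and k and on a common RR for both partner types. On the dichotomised endpoint the effect is limited to men staying classed as present.

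This should be put right before the first baseline assessment, because the classification cannot be repaired afterwards. It does not show that the trial would miss a benefit, and it does not bear on the stated sample size.

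**What to change.** In 4.3 and 4.9.3, state that a partner counts as HIV+ only if he disclosed it or his status was otherwise known, and that presumed status counts as unknown. Give the same written instruction at screening, baseline, post-intervention and 3 months, and apply it to the dichotomised fallback in 4.10.3.

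Prespecify total UAI with all male partners, summed from the by-status acts already collected, as a sensitivity analysis reported beside the primary endpoint. A fall in the primary endpoint with no fall in total UAI would then point to a shift between partner categories, which may be relabelling, disclosure or a real change in choice of partners. Total UAI should not replace the primary endpoint, since it includes acts with known HIV+ partners and would dilute an effect confined to the others.

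Cost: one questionnaire instruction, one extra table and somewhat higher baseline counts. Men whose only qualifying UAI was with presumed-HIV+ partners would also become eligible, and the team should accept that knowingly.
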